# Efficacy of exposure and response prevention therapy in mixed reality for patients with obsessive-compulsive disorder: study protocol for a randomized controlled trial

**DOI:** 10.1186/s40359-023-01116-3

**Published:** 2023-04-13

**Keywords:** CBT, Psychotherapy, OCD, Exposure therapy, Mixed reality, Augmented reality

## Abstract

**Supplementary Information:**

The online version contains supplementary material available at 10.1186/s40359-023-01116-3.

## Background

Obsessive-compulsive disorder (OCD) is a mental disorder characterized by intrusive thoughts (obsessions), and ritualized, repetitive behavior (compulsions) that aim to reduce negative feelings [2, 3]. It has a lifetime prevalence of 1–3% [4, 5], and often takes a chronic course if untreated [6]. Cognitive behavioral therapy (CBT) with exposure and response prevention (ERP) is the first line treatment for OCD, and is recommended by national and international guidelines [7]. In ERP the individual is exposed to stimuli, which trigger obsessions, compulsions or avoidance behavior. The goal of ERP is to confront feared objects or situations, without performing compulsions or avoiding the stimuli.

 Although ERP is highly effective, it is often not [8, 9] or incorrectly [10, 11] applied. Furthermore, only every third therapist or even less uses ERP *in vivo *[9, 12] and less than one third of those who practice ERP *in vivo* apply it according to the guidelines [12], leading to a serious treatment gap – the difference between the prevalence of a disorder and the treated proportion of affected individuals. A large longitudinal study conducted in the United States offers insight into the prevailing treatment gap. In total, 59% of patients with OCD were recommended CBT but only 44% received it [13]. According to a review from Kohn et al. [14] the treatment gap (i.e., untreated patients) in the United Kingdom is estimated between 60% and 68% and in the United States and Germany it is estimated at 59%, contributing to a rather low remission after treatment rate of 46.3% in Germany [15].

There are three main categories of treatment barriers concerning the treatment itself: the patient, the therapist and circumstances. While patients mainly fear being confronted with triggering stimuli during ERP [12], there are multiple treatment barriers on the therapists side, which impede the application of ERP. First, conducting ERP requires additional time (e.g., travelling to patients’ home), and therapists dread cancelled appointments [12] or terminated therapy [16–18]. Second, negative beliefs about ERP (e.g., harming the patient [19–23]) may discourage the therapist to conduct ERP. This dynamic often promotes hesitations to the application of ERP in the first place. Lastly, there exist other barriers such as the COVID-19 pandemic, which encourages social distance and hygiene, and thereby discourages ERP due to a possible risk of infection [24]. Guideline-based treatment therefore is often not or inadequately applied [15] and there is room for improvement. In order to increase the (correct) implementation of ERP and its initiation, we need to address the obstacles associated with its use. One option to increase the acceptance and feasibility of ERP may be the use of technical supported ERP. Here, the structure, mechanisms of ERP and potentially the high effects may be maintained.

### Technical supported exposure response prevention therapy

Technical supported therapy can be used to facilitate the application of ERP as it can address major treatment barriers of ERP *in vivo*: acceptability of treatment [25], a high variety of stimuli as well as improved control over the stimuli. Most studies have been conducted with virtual reality (VR) for anxiety disorders (for an overview, see Carl et al. [26]), for example, specific phobias [26, 27].

### Exposure therapy in virtual reality

Through VR glasses, the individual enters a virtual environment. In exposure therapy in VR (VRET) the individual is confronted with virtual three-dimensional presentations of triggering stimuli. This approach has been extensively studied in anxiety disorders, with at least similar positive effects when compared to exposure therapy *in vivo*. One meta analysis even found a small effect for VRET over *in vivo* (Cohen’s *d* = .35; [28]). Other meta analyses found similar effects [25, 26, 29, 30] for most anxiety disorders except for social anxiety disorder. Moreover, an early study [31] using VR for exposure therapy found that anxiety – measured with subjective units of distress (SUD) – followed the same curve of increase and decrease, such as in a study with fear of flying [32], but the overall anxiety level was less intense in VR. Further, emotions like anger and disgust – measured before and after the intervention – elicited by *in virtuo* and *in vivo *conditions, were not significantly different [33]. While the induction of fear seems similar, previous studies suggest that VRET is generally more accepted in anxiety disorders in contrast to exposure therapy *in vivo* [34, 35], whether this is also true for patients with OCD is still unclear.

### Exposure and response prevention therapy in virtual reality for obsessive-compulsive disorder

In OCD, research on the use of VR for ERP (VERP) is comparatively scarce, potentially due to its heterogeneity of symptoms (e.g., checking-, contamination- or sexual obsessions). A systematic review and recent meta-analysis on symptom and emotional response provocation using multiple kinds of VR-technology, mostly outside the context of ERP, however, supports that VR environments are generally able to provoke obsessive compulsive (OC) symptoms such as anxiety, disgust and the urge to wash in individuals with OCD compared to healthy controls [36], which argues for the feasibility of VERP. This is supported by findings from Miegel, Bücker et al. [37], who demonstrated that arousal due to disgust (measured with SUD) can be induced in VERP in patients with contamination-related OCD. So far, research on VERP for patients with OCD focused on investigating feasibility, evoking fear of contamination [38] and observing checking behavior [39–42]. Preliminary findings of VERP suggest feasibility [43, 44] and potential treatment efficacy [45], [38] and [37]. One recent study [46] investigated VRET in patients with contamination anxiety in an RCT comparing VRET to ERP* in vivo *with each 12 sessions and found a large effect in the reduction of OC symptoms (η_*p*_^*2*^ = .82). As findings stem from small or/and non-clinical samples, they need to be replicated in a representative randomized controlled trial (RCT). Moreover, Miegel, Bücker et al. [37] reported that sense of presence, which represents how present a person feels in a digital augmented environment, was only moderate in their VR environment, which was potentially due to unrealistic movement (a controller was used for teleportation).

### Exposure and response prevention therapy in augmented reality

Augmented reality (AR) glasses (e.g., Magic Leap 2) are much smaller and lighter compared to VR glasses. While looking through the glasses, individuals see their entire surrounding plus additional virtual objects that are projected into the real world. In AR, digital objects are anchored in the physical world, meaning, the digital and the real world are blended. In other words, the objects are “locked” in space as if they were a natural part of the real environment. Thus, the whole experience in AR may seem more real and the individual experiences a higher sense of presence, compared to VR. Also, patients can still see the therapist during ERP in AR, which might promote equally strong therapeutic relationships compared to ERP *in vivo* predicting a more favorable treatment outcome [47] and adherence [48]. AR has already been successfully integrated into medical training [49] and surgery simulation [50] and can be further used to guide implant placement in surgery [51].

By using AR instead of VR, realism and sense of presence could be enhanced. Realism describes the constructive process behind the creation of a person’s own current reality, which is a crucial element of sense of presence. In AR, sense of presence might be improved since the individual moves naturally instead of using a controller. As sense of presence determines how real a person feels in the virtual world, it may impact whether anxiety and disgust can be induced at a personal level and further determine the therapy outcome. Anxiety was able to be induced in AR in healthy individuals measured with self-reported and physiological parameter [52], though less studies are present for OCD. A recent study found that disgust can be induced in patients with OCD in AR and levels of sense of presence were positively related with higher level of anxiety [53]. The idea is based on the notion that anxiety and disgust needs to be inducible, as ERP is based on learning adaptive behaviour in response to triggering stimuli including the corresponding emotional response.

### Exposure and response prevention therapy in mixed reality

Mixed reality (MR) describes the spectrum of augmented reality and virtual experiences and is commonly used in interaction with devices such as the HoloLens or the Magic Leap. It allows the user to interact with real and virtual objects, while seeing their own body as well as the real surrounding at the same time. MR glasses use real time spatial mapping for merging real environments with digital objects and interaction with virtual objects without [54] and with a controller, though the stability of this tool without the controller is not yet established.

According to Hu et al. [55], MR has already been successfully integrated into the medical field (e.g., risk-free surgery training [56] and preoperative communication [57]). ERP in MR (MERP) might be especially relevant for the treatment of psychological disorders such as OCD, with its heterogeneous symptomatology. In MR, objects can be easily tailored to patients. The only preliminary evidence of acceptance of MR stems from research on technology acceptance of MR in museums [58], which notes that the technology is easy to use and highly engaging. According to our current knowledge, to date there is just our pilot study that investigates the feasibility and safety of applying MERP within a clinical sample [1]. 

In this study, we included a sample of *N* = 20 inpatients with contamination-related OCD [1]. During the intervention, all patients received standard care on the psychiatric ward and were randomly assigned to an add-on intervention (MERP + standard care) or control group (standard care only). Over the intervention period of three weeks, the intervention group received six sessions, including four sessions of MERP. For a detailed description, see Sect. 2.7.1. The pilot study [1] focused on safety and feasibility, thus was not powered and designed to investigate efficacy (small sample size and add-on design). Overall, the pilot study demonstrated safety and feasibility of MERP with no significant symptom deterioration in the intervention group. However, results on sense of presence and acceptance were mixed indicating that technical improvements were necessary. Improvement in the quality of the 3D graphics and the possibility of interaction in digital augmented realities are regarded as crucial for implementing a high sense of presence. We performed the necessary technical adjustments also incorporating the feedback of the therapists to investigate not only acceptance and feasibility but also the efficacy in the present RCT. Based on patients’ feedback, technical improvements were implemented and the list of virtual contamination-related objects has been extended (e.g., spray bottle, glass splinter). The planned RCT will be conducted with outpatients in order to be able to draw more robust conclusions.

The aim of the planned RCT is to test the efficacy of MERP in comparison to an active control group with regard to OCD symptomatology (Yale-Brown Obsessive Compulsive Scale [Y-BOCS; [59]), expectations of treatment success (expectations of the process and effectiveness of MERP) and acceptance of treatment (subjective appraisal rating), and feasibility (Temple Presence Questionnaire; TPI; [60]) of the revised MERP intervention. We hypothesize a larger reduction in both the primary outcome (OC symptom reduction according to the Y-BOCS) and secondary outcomes followed by high positive expectation ratings (> 75%) in both groups and subjective appraisal ratings (> 75%) in favor of the experimental group (MERP), in comparison to the active control group (self-guided application of ERP). Further, we postulate a larger decrease in depression (Beck Depression Inventory; BDI-II [61]), anxiety (Generalized Anxiety Disorder Scale-7; GAD-7 [62]), unwillingness to remain in contact with distressing emotions (Brief Experiential Avoidance Questionnaire; BEAQ [63]), state anxiety and distress (measured during MERP: distress ratings of the patient with Subjective Units of Distress; SUD; [64] and physiopsychological parameter: heart rate [puls], gaze fixation [eye-tracking] and skin conductivity [galvanic skin response]). Additionally, we expect symptom improvement from session one to session six in a variety of questions concerning multiple state sensitive dimensions of mental health (insession questionnaire, see supplementary material *C*). Further, we expect larger improvement in quality of life (WHOQoL-BREF global item) compared to the control group. To test these hypotheses, we plan to conduct an RCT with two parallel groups, both receiving active treatment (MERP or self-guided exposure).

## Methods

### Design

The present RCT will be assessor-blinded with parallel assignment to the MERP group and the active control group (self-guided exposure therapy, see German Registry for Clinical Studies [DRKS00020969]). The study includes a baseline and post assessment that takes place in person, a follow-up assessment by phone and an additional online survey, which participants complete at home before each in-person assessment and the telephone interview at follow-up. Participants will be randomized immediately after the baseline assessment. We offer a compensation of 50 Euros (total) for participitation in all three assessments. For an overview, see Table 1.

**Table 1 Tab1:** Standard protocol items: recommendation for interventional trials (SPIRIT) timeline

		Study Period				
	Enrolment	Allocation	Intervention period	Assessments		
TIMEPOINT**	*-t* _*0*_	0	*6 weeks*	*t* _*0*_	*t* _*1*_	*t* _*2*_
**ENROLLMENT**:						
***Eligibility screen***	X					
***Informed consent***				X		
***Primary measures***				X	X	X
***Secondary measures***				X	X	X
***Allocation***		X				
**INTERVENTIONS**:	MERP or self-guided exposure therapy					
***Intervention***			X			
***Self-guided exposure therapy***			X			
**ASSESSMENTS**:						
***Demographic interview***				X		
***M.I.N.I.***				X		
***Y-BOCS***				X	X	X
***Expectation of MERP***				X	X	
***Subjective Appraisal***					X	
***OCI-R***				X	X	X
***BDI-II***				X	X	X
***WHOQOL-BREF***				X	X	X
***GAD-7***				X	X	X
***TPI***					X	
***BEAQ***				X	X	X
***State sensitive questionnaire***			X			
***Further assessments during MERP (violation of expectancy and psychophysiological parameter) ***			X			
***SUD***			X			

M.I.N.I. = *Mini-International Neuropsychiatric Interview*, Y-BOCS = *Yale-Brown Obsessive Compulsive Scale*, OCI-R = *Obsessive Compulsive Inventory-Revised*, BDI-II = *Beck Depression Inventory*, WHOQOL-BREF = *World Health Organization Quality of Life-BREF (quality of life)*, GAD = *Generalized Anxiety Scale 7*, TPI = *Temple Presence Inventory*, BEAQ *= Brief Experiential Avoidance Questionnaire*, SUD *= Subjective Units of Distress*

### Sample size

No evidence is available for effects of MERP in contrast to an active control group without therapeutic guidance. Thus, we could only calculate sample size approximately. We expect a large effect based on a meta-analysis investigating VRET in anxiety disorders, which found a medium to large effect of VRET compared to an active psychological control condition (*Hedges g* = 0.80; [26]). We expect the effect of MERP to be even higher than in VERP since our technique is more advanced and may induce higher sense of presence, which may have a positive effect on mechanisms like arousal induction [36, 65, 66].

The power analysis (calculated with G*power; [67]) determined a sample size of 64 participants to detect a large effect (*f* = 0.4, α = .05, power of .80).

### Recruitment

Participants will be recruited using contact forms from previous studies of our working group and through advertisement (e.g., newspaper articles, OCD support groups; leaflets; network of therapists; Google AdWords; Facebook and Instagram). A landing page (www.uke.de/zwang_mr) and a flyer will be used for recruitment.

### Inclusion and exclusion criteria

We will recruit outpatients with OCD. The diagnosis of OCD will be confirmed by the Mini-International Neuropsychiatric Interview 7.0.2 (M.I.N.I.: [68]; German version: [69]), that is based on the Diagnostic and Statistical Manual of Mental Disorders (5th ed.; DSM-5) and the content of OCD (contamination-relation) will be assessed by the Yale-Brown Obsessive-Compulsive Scale; Y-BOCS [59, 70]. Further psychiatric diagnoses for in- and exclusion criteria will be verified with the M.I.N.I. interview. Participants have to fulfill the following criteria:

#### Inclusion criteria

the presence of contamination-related obsessions and compulsionsprovision of informed consentage between 18 and 80 yearssufficient command of the German languagewillingness to participate in MERP or self-guided exposure for six weeks

#### Exclusion criteria

a past or present diagnosis of schizophrenia or bipolar disordera present severe substance use disorderacute suicidalitya severe neurological disorder associated with OCDcurrent inpatient treatment (including day care treatment)

### Randomization and assessor blindness

The randomization will be administered by the principal investigator by using an online randomization software (https://miniwebtool.com/de/number-randomizer/). The participants will be randomized either to MERP or the self-guided exposure therapy. When a participant enters the study, she/he will receive the consecutive identification number. The participant will be randomized after baseline assessment. All assessors are blinded and will not be informed about group allocation. Unplanned unblinding will be documented.

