### Procedure

Patients eligibility will be checked within a telephone interview. Eligible patients will be invited for the baseline in-person interview. The participants receive detailed information about the study and informed consent will be provided by the interviewer. The online survey will be provided before each interview. Demographic information, psychiatric diagnoses (M.I.N.I.) and OC symptoms (Y-BOCS) will be assessed in-person. After the baseline interview (t0), participants will receive an envelope, which includes information about the group allocation. During the following six weeks, participants will receive MERP once a week or conduct self-guided ERP based on a manual they receive shortly after the interview by the principal investigator. Patients will be asked to send back the manual to the office before the post assessment, which will maintain the allocation blinding of the interviewer. Both groups will attend the in-person post assessment after six weeks (post assessment; t1) and a telephone interview three months (follow-up; t2) after the post assessment, whereby the Y-BOCS will be administered again. Before, during and after each session (MERP or self-guided exposure), multiple parameters (e.g., physiopsychological parameter [only in MERP], state sensitive questions [see supplementary material *C*] and SUD) will be assessed.

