### Trial status

The first participant was enrolled in March 2022. At present, 30 participants attended their baseline assessment. At the time of submission of this study protocol, participants were still being recruited, and no data had been extracted and analyzed yet. All future changes to the study protocol will be recorded in an independent amendment. SPIRIT guidelines were followed for the whole article.

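### Randomization is run by the principal investigator, who is not independent of trial conduct, on a public number page, and no described step hides the next assignment from that person or prevents a re-draw

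*Protocol article*

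**What the plan says.** All references are to the protocol article.

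- **Who randomizes, and with what** (Randomization and assessor blindness): "The randomization will be administered by the principal investigator by using an online randomization software". The link that follows leads to a generic number-randomizer page.
- **What is assigned** (same section): "The participants will be randomized either to MERP or the self-guided exposure therapy". Participants are numbered on entry: "When a participant enters the study, she/he will receive the consecutive identification number".
- **When** (Design): "Participants will be randomized immediately after the baseline assessment".
- **How the result reaches the participant** (Procedure): after the baseline interview, "participants will receive an envelope, which includes information about the group allocation".
- **Who supplies the control treatment** (Procedure): the self-guided arm follows "a manual they receive shortly after the interview by the principal investigator".
- **Blinding** (Randomization and assessor blindness): "All assessors are blinded and will not be informed about group allocation". Under Procedure, the manual is to be returned before the post assessment so that the interviewer stays blind.
- **Progress** (Timetable and research plan; Sample size): 30 randomized, 64 planned.

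**The concern.** A randomized comparison is protected at entry only if whoever can affect an assignment neither knows nor can change it. Here that person is the principal investigator, who also delivers part of the trial. The team holds a directional expectation: the aims at the end of the Background predict an advantage for MERP, and the Sample size section expects an effect larger than that seen with virtual reality.

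If assignments could be foreseen or repeated, participants judged more suitable, for example more motivated for exposure, could be steered to one arm. That would affect the Y-BOCS result and every secondary outcome together. The planned ANCOVA adjusts for the baseline score of the outcome being analysed. It cannot correct for selection on features that are not measured or not in the model. Nothing in the article suggests that this has happened. The issue is whether the described method would let the team show that it did not.

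**Working it through.** The article gives no figure on this point, so the check sets its statements side by side.

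**Step 1. Is the person controlling allocation independent?** The Randomization section names the principal investigator. The Procedure section links the principal investigator to the manual or, if the sentence is parsed differently, to the interview. The second parsing is hard to sustain: the interviewer is to remain blind, and the person who administers randomization cannot be. The natural reading is therefore that the principal investigator gives controls their manual. On either parsing the person has a role in trial conduct.

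**Step 2. Two ways the web page could be used.** The text fits both.

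| Possible procedure | What would need guarding | Is a guard described? |
|---|---|---|
| A separate draw for each participant after t0 | A result could be discarded and drawn again | No |
| A list generated in advance | The list holder knows the next assignment | No; no holder other than the principal investigator is named |

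The two exposures belong to different procedures and should not be charged together. Under either one, the principal investigator could know or change an assignment.

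**Step 3. What each stated safeguard covers.**

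- *Randomization after baseline.* This is good practice. It keeps the baseline ratings free of knowledge of the arm. It does not bear on whether a draw can be repeated.
- *Envelope.* It is described as the way the participant learns the allocation. The article does not say who fills it, when, or whether it is sealed, so it is not described as hiding anything from the principal investigator.
- *Consecutive number.* It fixes the order of entry. The article does not tie it to a sequence set beforehand, which is what would make a re-draw visible.
- *Assessor blinding.* It protects outcome rating at t1 and t2, not the formation of the groups.

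**Step 4. How much of the trial can still be changed.** Planned 64 − randomized 30 = 34 remaining, or 34/64 = 53% of the planned sample. The count of 30 is the one given in the article, so the number left at the time of any change may be smaller.

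**The case against.** The strongest reply is that this is a condensed article. Sequence restriction, custody of the list and logging are commonly left to the full protocol, and their absence here is not a finding. That stands. A reader might infer from the text that allocation is unconcealed, unblocked and without an audit trail, or that the principal investigator draws each assignment singly. The article says none of these things; all four come from silence. Concern about unequal arms falls with them, because it needs unrestricted allocation, which is not stated.

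Two further replies also have force. No section says that the principal investigator screens, consents or enrols: eligibility is checked by telephone and consent is handled by the interviewer. A claim that the timing of entry could be influenced therefore has no direct support. Handing over the manual happens after assignment, so it is not itself a route for altering an assignment. It shows only that the principal investigator is unblinded and involved.

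What these replies do not remove is the stated choice of person and tool. A fuller document could add safeguards around that choice, but it could not make the principal investigator independent without contradicting the article.

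**Conclusion.** The point holds in limited form. The article fixes allocation in the hands of a principal investigator who is not independent of trial conduct, using a generic public page. None of its stated safeguards is described as concealing the next assignment from that person or as preventing a re-draw. By the method described, selection at allocation is not guarded against.

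The size of any bias cannot be estimated from the article, and no misconduct is implied. It would also go too far to say that allocation can never be verified, because whether records exist is unknown. The conclusion rests on two assumptions: the natural reading of the manual sentence, and no unshown document placing custody of the sequence elsewhere. If such custody exists, the remedy reduces to stating it. The change is worth making because about 34 of 64 assignments were still to come and randomization underlies every comparison.

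**What to change.** For the remaining participants:

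1. Have the sequence generated in advance, archived, and held by an existing colleague with no role in recruitment, treatment or assessment, or by an institutional randomization system if there is one. The article does not state the ratio; 1:1 is assumed here and should be confirmed.
2. Release each assignment by consecutive ID in a sealed envelope, only after t0 is complete. The numbering and envelopes are already in use.
3. Write down how the first 30 were allocated: single draws or a list, who made them, and what output was kept.
4. Record the change through the amendment route given under Trial status and Ethical standards, including the trial registration.

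The cost is a small amount of an existing colleague's time and a mid-trial amendment. Allocation will then have been handled in two ways within one trial, which the report should state.
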